### Recruitment

Patients listed for a routine primary TKR under the care of the participating surgeons will be screened by the treating clinician. A screening form will be completed to confirm name, age, hospital number, listed for routine primary TKR, suitable candidate for a cruciate retaining TKR (Triathlon prosthesis), no varus deformity of > 20°, capacity to provide informed consent and no pre-existing condition that limits function and potential outcome of surgery. After making the initial approach, the consultant will request the patient’s permission to be approached by the research team who will provide the patient information sheet, discuss the study in more detail and confirm eligibility. Patients will be encouraged to take the study information and discuss with their family and friends before making a decision to participate. The research team will reconfirm the eligibility criteria below and record that: the patient is able to comply with the study protocol (incl. refusal for CT scan) and that female participants are not pregnant, lactating or planning pregnancy during the course of the study.

Eligible patients are identified by the treating consultant surgeon and listed for surgery and a screening form is completed but are not approached at that time will be sent a letter of approach from the consultant along with the patient information sheet. The research team will then contact the patient to discuss the study in more detail and answer any questions. All eligible patients who agree to participate in the study will be invited to attend a research clinic to provide written informed consent and complete baseline assessments before randomisation.

Participants will be asked to attend a research appointment to provide written informed consent and complete a CRF and a number of pre-operative questionnaires recording their knee function, expectations and general health. Participants will be asked to carry out a gait assessment which involves walking over an instrumented walkway (Tekscan instrumented mat system, Tekscan Inc. Boston, USA) that is 3 m long plus 1 m either side, six times and standing still on an individual instrumented mat of the walkway for 1 min. After completing the baseline assessments participants will be randomised to one of two groups. Patients will be informed of their allocation and the research staff will reinforce the treatment allocation and arrange a CT for those randomised to the intervention group.

All participants will attend a routine pre-assessment clinic 4–6 weeks prior to surgery to assess fitness for surgery. Pre-assessment staff will be notified of the patient’s inclusion in the study and their group allocation. Participants randomised to the robotic-assisted surgery group will be required to have an additional CT scan which may be arranged to coincide with this appointment. At this routine clinical appointment, the research team will ensure all baseline data is complete and ensure the patient has no concerns. The CT scan will be anonymised using a dedicated study code and transferred to Stryker using an encrypted data drop box. The CT scan will be reconfigured and transferred back using an encrypted data drop box. This data will be used by the MAKO technician to plan the individuals’ surgery. This process is standard practice in hospitals across the UK already using the MAKO for robotic-assisted knee surgery.

All participants will be admitted in line with routine practice. Surgical data and hospital discharge data will be collected from source data to complete the CRF during the inpatient stay. No additional research assessments will be carried out at this point.

All participants will attend a routine 3-month post-surgery assessment with the clinical team including knee radiographs. Participants will also be seen by the research team to complete the relevant patient-reported questionnaires, Health service resource use and complications data forms.

All participants will be asked to attend an additional 6-month post-surgery research visit to complete the relevant patient-reported questionnaires, health service resource use and complications data forms. The gait assessment carried out at baseline will be repeated.

A member of the research team will contact the participant by telephone at 9 months following surgery to complete the health service resource use questionnaire as this only captures data over the previous 3 months.

All participants will attend a routine 12-month post-surgery assessment with the clinical team including knee radiographs. Participants will also be seen by the research team to complete the relevant patient-reported questionnaires, health service resource use and complications data forms. A gait analysis assessment will also be carried out.

### Consent

Written and verbal versions of the participant information and informed consent will be presented to the participants by the research team. This will explain no less than the exact nature of the study, the implications and constraints of the protocol and any risks involved in taking part. It will be clearly stated that the participant is free to withdraw from the study at any time for any reason without prejudice to future care, and with no obligation to give the reason for withdrawal. The participant will be encouraged to take the study information home and have the opportunity to question the Investigator, their GP or other independent parties to decide whether they will participate in the study.

Participants who decide to take part will be invited to an additional research visit to provide written informed consent. Written informed consent will be obtained by means of participant dated signature and dated signature of the person who presented and obtained the informed consent. The person who obtained the consent will be suitably qualified and experienced member of the research team and have been authorised to do so by the Chief/Principal Investigator. Copies of the signed informed consent will be given to the participants as well as filed in the medical notes. The original signed form will be retained at the study site in the TMF.

The participant must personally sign, print their name and date the latest approved version of the informed consent form before any study-specific procedures are performed. If for whatever reason the patient is unable to print their name or date the consent form, this can be completed by the researcher taking consent, at the patient’s request. It must be fully documented on the consent form that the researcher has taken this action, with the reason why also documented. However, the researcher must *not* sign the consent form on behalf of the patient; the patient must always sign the consent form.

### Allocation

Patients are allocated once they have been screened and have given informed consent to participate in the trial. Subject numbers will be assigned sequentially as each subject enters the study. Participants will be randomised on a 1:1 ratio using the Sealed Envelope software (www.sealedenvelope.com) after consent and baseline data collection is complete to reduce the risks of selection bias. Randomisation will be carried out in random sized equally split blocks to allow even balancing of the groups and avoid selection potential bias. Patients will be allocated to standard treatment (manual TKR) or intervention group (robotic-arm- and sensor-assisted TKR). It will not be possible to conceal the allocation of treatment from the patient, or the clinicians. Research staff completing follow-up assessments and data analysts will be blinded to the participant’s allocation to reduce potential bias.

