The majority of TKR are performed manually by the surgeon using jig-based systems and the knee is balanced by the ‘feel’ though a range of movement. It is recognised that manually performed TKR are misaligned in up to 30% of patients and during the saw cuts soft tissues around the knee may be damaged [14], which can disrupt the balance of the knee. In addition, the definition of a balanced TKR is variable and is dependent upon the surgeons ‘feel’ and hence is not a consistent measurable variable [15]. The Verasense^TM^ (OrthoSensor Inc. Dania Beach, FL, USA) enables the surgeon to objectively balance the TKR through soft tissue releases intra-operatively according to pressure readings within the knee, which has been shown to significantly improve the rate of patient satisfaction [8, 16].

The robotic-arm-assisted TKR has been demonstrated to be 100% accurate in achieving the planned alignment of the knee prosthesis [17], and the Verasense^TM^ (OrthoSensor Inc. Dania Beach, FL, USA) enables the surgeon to objectively balance the TKR with release of the peri-articular soft tissues or further bone cuts [8, 16]. It is hypothesised that robotic-assisted TKR will optimally align the prosthesis and the Verasense^TM^ (OrthoSensor Inc. Dania Beach, FL, USA) will balance the knee with releases of the peri-articular soft tissues which will result in an improved patient outcome when compared to conventional manual TKR.

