### Eligibility criteria

Participants listed for routine primary TKR for osteoarthritis under the care of the two participating surgeons at the institution will be screened for inclusion. The inclusion criteria are as follows: planned to undergo a primary TKR for end-stage osteoarthritis under the care of the two participating surgeons, age 45–85 at the time of listing for surgery, and suitable candidate for a cruciate retaining TKR (Triathlon prosthesis). The exclusion criteria are as follows: varus deformity of > 20° observed by consultant on examination, patient is unable to comply with the study protocol (incl. refusal for CT scan), female participants who is pregnant, lactating or planning pregnancy during the course of the study, requires patella resurfacing, inability to understand the patient information for the study, provide written informed consent or answer study questionnaires for cognitive or language reasons, or any other significant disease or disorder which, in the opinion of the Investigator, may either put the participants at risk because of participation in the study or influence the result of the study, or the participant’s ability to participate in the study.

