An economic evaluation will be conducted from an NHS perspective. Data collection from the study will also focus on estimating the cost of the interventions and subsequent use of services. Analyses will be carried out from an NHS perspective and will include the capture of resource use from secondary and primary/community care. All relevant costs associated with providing the interventions will be included including length of stay. All unit costs will be derived using routine data sources and study specific estimates. Costs in the follow-up period will include use of secondary care services, e.g. inpatient stays and outpatient visits, and primary/community care services, e.g. general practice visits, district nurse visits and prescription costs incurred over the follow-up period. This data will be collected using a health service utilisation patient diary. Data on use of services will be combined with appropriate unit costs to produce a cost for each trial participant. From these, a mean cost per intervention will be calculated. Health-related quality of life will be measured using EQ-5D-3L which is a very simple measure which patients complete at the start and end of treatment. It comprises five dimensions of health: mobility, ability to self-care, ability to undertake usual activities, pain and discomfort, and anxiety and depression. The cost-effectiveness analysis of the two types of surgery will be based on incremental cost of a quality-adjusted life year (QALY). QALYs will be estimated using the area under the curve approach. The results will be presented as point estimates of mean incremental costs and QALYs. The results of the analyses will include deterministic and stochastic sensitivity analysis, presented as point estimates and cost-effectiveness acceptability curves (CEACs).

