### Sample size

A power calculation was performed using the functional component of the WOMAC [18] as the primary outcome. Using the defined minimal clinically important difference in the WOMAC of 15 points [33], a standard deviation (SD) of 26.5, and an alpha 0.05 with a power of 80% to demonstrate a superior outcome in the intervention group (one tailed analysis), it was determined that 80 patients would need to be recruited (40 in each arm). Loss to follow-up data from other surgical arthroplasty studies in the institution with a similar follow-up regime were used to estimate a loss to follow-up of 10%. On this basis, 90 patients will be randomised to ensure the study achieves power.

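### The Allocation section names no stratification by surgeon, so the two surgeons' patients can split unevenly between arms by chance: a modest but avoidable loss of precision and clarity

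*Protocol article*

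**What the plan says.** The protocol article's Allocation section gives the method and its purpose. "Participants will be randomised on a 1:1 ratio using the Sealed Envelope software", after consent and baseline assessment, and "Randomisation will be carried out in random sized equally split blocks to allow even balancing of the groups and avoid selection potential bias". No stratification or minimisation factor is mentioned.

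The Eligibility criteria section restricts the trial to patients listed for primary knee replacement "under the care of the two participating surgeons". Each patient's surgeon is therefore fixed at listing, before randomisation.

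The Background section says that what counts as a balanced knee is variable and "dependent upon the surgeons ‘feel’ and hence is not a consistent measurable variable". The Surgical intervention section has the manual arm balanced that way, and the robotic arm balanced to a sensor pressure threshold.

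The Statistical analysis section compares groups by parametric or non-parametric tests and analyses changes in the key outcomes by ANOVA. The only adjustment it names is for multiple testing. For costs, after building a cost for each participant, it says: "From these, a mean cost per intervention will be calculated". No surgeon term appears in any of these analyses.

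**The concern.** Permuted blocks without strata force the two arms to near-equal size. They do nothing to equalise how many of each surgeon's patients fall in each arm. With only two surgeons, one of them could by chance operate on a clearly larger part of one arm.

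Surgeon is the natural factor to balance here. It has two levels, is known before randomisation, and needs no extra data. The trial's rationale also treats the surgeon's judgement in balancing the knee as a source of variation. If the two surgeons' results differ, an uneven split moves every comparison that ignores surgeon. A reader of the results would then ask how much of an observed difference reflects the device package and how much the surgeon mix.

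**Working it through.** **The plan's own figure.** The Sample size section gives a difference of 15 points, "a standard deviation (SD) of 26.5, and an alpha 0.05", 80% power and a one-tailed test.
- Normal approximation: n per arm = 2 × (1.645 + 0.842)² × (26.5/15)² = 38.6, so 39.
- The t-based version gives 39.3, so 40 per arm and 80 in total, as stated.
- With 10% loss: 80/0.9 = 88.9, so 89, against 90 randomised.

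The stated size reproduces, and stratifying by surgeon would not change it. The article states no figure for surgeon balance.

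**Chance imbalance without strata.** Take 90 patients, 45 per arm, with K belonging to surgeon A. The caseload is not given, so K = 45 and K = 60 are assumptions. The number X of surgeon A's patients in one arm is treated as hypergeometric:

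Var(X) = 45 × (K/90) × (1 − K/90) × (45/89)

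The between-arm difference in surgeon A's share is (2X − K)/45, with SD = 2 × SD(X)/45.

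| Caseload | Var(X) | SD of share difference | P(gap ≥ 15 points) | P(gap ≥ 20 points) |
|---|---|---|---|---|
| 45/45 | 5.69 | 10.6 points | 20.6% | 9.1% |
| 60/30 | 5.06 | 10.0 points | 11.7% | 4.3% |

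Simulating random permuted blocks (sizes 2/4/6 and 4/6/8, assumed), with surgeon varying from patient to patient, gives the same SDs. The chance of a gap of at least 20 points is then about 7% at an expected 50:50 caseload and 5% at 67:33. It differs slightly from the exact values because the caseload also varies in the simulation.

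**What that does to the primary comparison.** If the surgeons' mean WOMAC function change differs by d in both arms, the shift is the share difference × d. The document gives no value for d; assume 10 points (range 5 to 15).
- A 20-point gap shifts the arm difference by 0.20 × 10 = 2 points (1 to 3 over the range), against the 15-point planning difference and the 9 points raised in the Discussion.
- SD of the shift over all possible allocations: 0.106 × 10 = 1.06 points (45/45), or 0.100 × 10 = 1.0 point (60/30).
- Standard error of the arm difference: 26.5 × √(2/45) = 5.59, or 26.5 × √(2/40) = 5.93 with 40 per arm.
- Share of variance at 45 per arm: 1.06²/5.59² = 3.6%, or 1.0²/5.59² = 3.2%. At 45/45, d = 5 gives 0.53²/5.59² = 0.9% and d = 15 gives 1.59²/5.59² = 8.1%.

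**With blocks run within surgeon.** If the largest block is 6, each surgeon's patients differ between arms by at most 3, so the share gap is at most about 3/45 = 6.7 points. With a largest block of 8 it is at most about 4/45 = 8.9 points. In simulation the SD falls below 2 points and no gap reaches 10.

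**The case against.** **The article is condensed.** It does not say that a single list is used, and random-sized, equally split blocks could be run within surgeon. The full protocol is not shown. This stands: the point rests on a section that describes the method and names no factor, so the fix must be conditional.

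**The design is valid as described.** Unstratified blocked randomisation is unbiased in expectation and keeps its alpha. A reader might infer that the trial is confounded by surgeon, or that it fails its own aim of evenly balanced groups. Neither is supported. The stated aim fits numbers per arm, which blocks deliver, and the article never promises balance on surgeon.

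**The surgeon effect is assumed.** The article gives no difference between surgeons on any outcome. It also describes much standardisation: the same implant, the same jig technique and fixed resections in the manual arm, prespecified cuts and a pressure target in the robotic arm, and common inpatient care and rehabilitation. Balancing by feel is confined to the manual arm. If the effect sat only there, a 20-point gap would move that arm's mix by about 10 points from 50:50, and the shift would be 0.10 × 10 = 1 point rather than 2. All of this limits the size; none of it removes the imbalance.

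**Surgeon mix could still be examined.** A reader might infer that an uneven split would affect all outcomes as raw means and could not be disentangled. A raw mean per arm is stated only for cost. Surgeon is known for every patient, so a table or an adjusted analysis can separate it, and an analysis plan not shown may already include such a term.

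**Stratifying has a price.** Clinicians know the allocations, and blocks within surgeon give each surgeon a shorter, slightly more predictable sequence. This stands as a small cost.

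**Conclusion.** The point holds as a modest design improvement. As described, allocation leaves the surgeon mix to chance, with an SD of about 10 to 11 percentage points between arms and a 4 to 9% chance of a gap of 20 points or more for caseloads from 60/30 to 45/45. Under an assumed 10-point surgeon difference this adds about 1 WOMAC point of SD, or 3 to 4% of the variance of the arm difference. That is imprecision already contained in ordinary chance error, not bias. It is worth removing because it is cheap to avoid, and because a two-surgeon trial whose stated analyses carry no surgeon term invites the question of surgeon mix.

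The figures depend on the assumed caseload split and surgeon effect. The conclusion depends on the full protocol not already stratifying by surgeon.

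**What to change.** First check the full protocol and the randomisation settings. If surgeon is already a stratum, say so in the Allocation section and nothing more is needed on allocation.

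- **If recruitment is open:** set participating surgeon as a two-level stratification factor in Sealed Envelope, keep random block sizes within each stratum, and include surgeon in the analysis.
- **If recruitment is closed:** prespecify surgeon as a fixed factor in the outcome and cost comparisons. The Trial status section estimated the end of recruitment as May 2021, so this may be the only option. Stratifying cannot help patients already randomised.
- **In either case:** report the surgeon-by-arm table.

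The cost is one system setting and a short amendment, one or two more unfinished blocks, and slightly more predictable runs per surgeon, which random block sizes mitigate. The target of 80 evaluable and 90 randomised patients is unchanged.

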### Outcome measures

The primary goal of joint replacement surgery is to restore function and reduce pain, the outcome measures have been chosen to reflect these factors. The primary outcome will be changed in functional ability measured by the WOMAC [18] questionnaire from baseline to 6 months following TKR. The WOMAC^18^ questionnaire consists of 24 self-administrated questions with pain, stiffness and function subscales. The score is validated for patients with knee OA to detect changes in functional ability.

The following outcome measures will be used to assess changes in activity levels, joint awareness, and satisfaction and health status as secondary outcomes. Change in activity participation from baseline to 3, 6 and 12 months following knee replacement will be assessed using the OKS [19] which consists of twelve questions assessed on a Likert scale with values from 0 to 4; a summative score is then calculated. In addition, a higher functioning supplementary questionnaire consisting of a further eight questions will be used. This was designed to assess activity participation for patients that may achieve the ceiling score in the OKS [25]. Change in joint awareness from baseline to 3, 6 and 12 months following knee replacement surgery will be assessed using the FJS which is designed to assess joint awareness in hips and knees during various activities of daily living [20]. It uses a 5-point Likert response format, consisting of 12 equally weighted questions with the raw score transformed to range from zero to 100 points. In previous studies, the score has shown good reliability and convergent validity [20], performed well in known-group comparisons, and was found to be sensitive to change over time [26]. Patient expectation pre-operative and fulfilment will be assessed at 3, 6 and 12 months following knee replacement surgery. The HSS is a validated measure of patient pre-operative expectations of surgery [21, 22, 27]. The level of patient expectation is indicated on a 5-point Likert scale as ‘very important’, ‘somewhat important’, ‘a little important’, ‘I do not expect this’ or ‘this does not apply to me’ [21]. After surgery, patients will complete a similar expectation questionnaire, but are asked whether the same expectations had been fulfilled, which again is assessed on a 5-point Likert scale as ‘greatly’, ‘a lot’, ‘a little’, ‘I did not expect this’ or ‘this did not apply to me’ [22]. Patient satisfaction at 3, 6 and 12 months following hip replacement surgery and will be assessed following surgery by asking four questions with a different focus:
‘Overall how satisfied are you with the results of your hip replacement surgery?’‘How satisfied are you with the results of your hip replacement surgery for improving your ability to do housework or yard work (such as cooking, cleaning, or gardening and raking leaves)?’‘How satisfied are you with the results of your hip replacement surgery for improving your ability to do recreational activities (such as taking walks, swimming, bicycling, playing golf, dancing, going out with friends)?’‘How satisfied are you with the results of your hip replacement surgery for relieving your pain?’

The response to each question will be recorded using a 4-point Likert scale: very satisfied, somewhat satisfied, somewhat dissatisfied and very dissatisfied. These questions and the 4-point Likert assessment have been validated and demonstrated to be reliable to measure satisfaction following primary hip replacement surgery [23]. Change in pain, stiffness, and functional ability from baseline to 3, 6 and 12 months following surgery will be assessed using the subscales of the WOMAC [18] questionnaire. Change in patient-reported quality of life from baseline to 3, 6 and 12 months following knee replacement surgery will be assessed using the EQ-5D-3L general health questionnaire [28] which evaluates five domains (-5D), which include mobility, self-care, usual activities, pain/discomfort and anxiety/depression. This is a two page questionnaire that consists of five dimensions, with the responses recorded at three levels (3L) of severity (no problems, some problems or extreme problems). The second page consists of a standard vertical 20cm visual analogue scale (EQ-5D VAS) which is transformed to a scale of 0 to 100 measuring current health-related quality of life. Each patient’s health state, derived from the EQ-5D, will be measured before and after their surgery to determine the change in their health gain or loss after their knee replacement surgery. The health state will then be multiplied by the time spent in that state to derive the QALYs gained or lost. The cost per QALY will then be calculated by dividing the cost of the procedure by the QALYs gained after TKR.

A cost-utility analysis will be undertaken from a UK NHS perspective up to 12 months following knee replacement and also projected over 5 and 10 years and a lifetime horizon. A health service resource use questionnaire will be completed by the patient at the 3-, 6- and 12-month research assessment. The questionnaire collects data on primary, secondary and community care and associated with the knee replacement over the previous 3 months. An additional telephone follow-up will be carried out at 9 months where the research team will complete the questionnaire with the participant to ensure the data is complete for the 12-month follow-up period. Inpatient and surgical data will be collected on the case report forms (CRFs) and complications will be recorded at each visit.

Gait patterns will be analysed at baseline and 3 months following surgery. Participants will complete a gait assessment to record spatiotemporal characteristics of their walking pattern prior to surgery. The gait assessment will consist of the patient walking over a 3-m instrumented walkway (Tekscan Inc., Boston, USA), including a metre at either end of the walkway to allow for acceleration and deceleration, a total of 5 m.

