**Methods and analysis:**

This randomised controlled trial will include 90 patients with end-stage osteoarthritis of the knee undergoing primary TKR. Patients meeting the inclusion/exclusion criteria that consent to be in the study will be randomised at a ratio of 1:1 to either manual TKR (standard of care) or robotic-arm-assisted TKR with Verasense^TM^ to aid balancing of the knee. The primary objective will be functional improvement at 6 months following surgery between the two groups. The secondary objectives are to compare changes in knee-specific function, joint awareness, patient expectation and fulfilment, satisfaction, pain, stiffness and functional ability, health-related quality of life, cost-effectiveness, and gait patterns between the two groups. Ethical approval was obtained by the Tyne & Wear South Research Ethics Committee, UK. The study is sponsored by the Newcastle Hospitals NHS Foundation Trust.

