## Methods/design

### Objectives

The primary aim is to compare change in functional ability (measured by the functional component of the Western Ontario and McMaster Universities Osteoarthritis Index (WOMAC) [18]) from baseline to 6 months (early) following TKR between the two groups. The secondary outcomes are:
To compare changes in knee function in activities of daily living (measured by the Oxford knee score (OKS) [19]) from baseline to 3, 6 and 12 monthsTo compare changes in joint awareness (measured by the Forgotten Joint Score (FJS) [20]) from baseline to 3, 6 and 12 monthsPre-operative patient expectation and fulfilment at 6 and 12 months will be assessed using the Hospital for Special Surgery Knee Replacement Expectations Questionnaire (HSS) [21, 22]To compare satisfaction using a validated outcome measure at 3, 6 and 12 months [23]To compare pain, stiffness and functional ability (measured by the WOMAC [18]) at 3, 6 and 12 monthsTo compare the health related quality of life using the Euro Qol five dimensional (EQ5D-3L) [24] at baseline and 3, 6 and 12 monthsTo compare the cost effectiveness of the two interventions from a UK NHS perspectiveTo analyse any differences in gait patterns between the two groups

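### The satisfaction outcome of this knee trial is worded for hip replacement, and its validation is stated only for the hip

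*Protocol article*

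**What the plan says.** **Population.** The abstract (Methods and analysis) states "This randomised controlled trial will include 90 patients with end-stage osteoarthritis of the knee undergoing primary TKR". The Eligibility criteria require that the patient is "planned to undergo a primary TKR for end-stage osteoarthritis under the care of the two participating surgeons". The Surgical intervention section gives all participants the same knee prosthesis. There is no hip replacement arm or subgroup.

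**Outcome.** Satisfaction is listed as a secondary outcome in the Objectives: "To compare satisfaction using a validated outcome measure at 3, 6 and 12 months", citing reference 23.

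**Definition.** The Outcome measures section introduces it as "Patient satisfaction at 3, 6 and 12 months following hip replacement surgery" and says that it will be assessed by asking four questions, each printed in quotation marks:
- overall: "Overall how satisfied are you with the results of your hip replacement surgery"
- household tasks: "How satisfied are you with the results of your hip replacement surgery for improving your ability to do housework or yard work"
- recreation: "How satisfied are you with the results of your hip replacement surgery for improving your ability to do recreational activities"
- pain relief: the fourth item, which again asks about hip replacement surgery.

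**Validation.** The same section says that the items and their 4-point scale have been "validated and demonstrated to be reliable to measure satisfaction following primary hip replacement surgery", again citing reference 23.

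**The concern.** The text that defines the outcome names an operation that the trial does not perform. A single slip would be trivial. Here the lead-in, all four items and the validation sentence agree with one another and disagree with the rest of the article, and the items are set out as the questions to be asked. Someone building or checking the form from this text would ask knee patients about a hip operation.

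A second problem sits beside the first. The Objectives call the measure validated without naming a joint, and the only support given is for the hip. As written, the article offers no support for validity after knee replacement, and correcting the four items alone would not change that.

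Satisfaction is not a peripheral outcome here. The Background motivates the trial with the 10 to 20% of knee replacement patients who are not satisfied, and it credits the sensor with improving satisfaction. The Discussion lists satisfaction among the outcomes to be quantified. If hip-worded items reached patients, some answers would be hard to interpret: an item might be left blank, or answered about a previous hip operation, which the Eligibility criteria do not name as an exclusion.

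**Working it through.** The plan gives no figure to reproduce. The check is a comparison of wording, followed by a count.

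**1. Which joint each part of the satisfaction definition names (Outcome measures)**

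| Part of the definition | Joint named |
|---|---|
| Lead-in sentence | Hip |
| Item 1, overall | Hip |
| Item 2, housework or yard work | Hip |
| Item 3, recreation | Hip |
| Item 4, pain relief | Hip |
| Validation sentence | Hip |

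The hip is named 1 + 4 + 1 = 6 times and the knee not once. Of the four items, 4 name the hip and 0 name the knee.

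**2. Which joint the neighbouring outcomes name.** In the same section, the Oxford knee score, the Forgotten Joint Score, the expectation questionnaire and the EQ-5D-3L are each tied to follow-up after knee replacement. The satisfaction block is the exception.

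**3. Whether another mention of the hip explains it.** The Background mentions the hip because the planning CT covers hip, knee and ankle. The Outcome measures section mentions it because the Forgotten Joint Score was designed for both joints. Both uses are legitimate, and neither bears on the satisfaction items.

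**4. Validation.** The Objectives say validated and name no joint. The Outcome measures section says validated for the hip. Both cite reference 23, which is not available here, so the joint it covers cannot be settled from the article.

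**5. Upper limit on the responses involved, if the form carries the printed wording.** Inputs: 4 items (Outcome measures), 3 visits at 3, 6 and 12 months (Objectives), 90 randomised and 10% expected loss (Sample size).
- Per patient: 4 × 3 = 12 responses.
- Full follow-up: 12 × 90 = 1,080.
- With 10% lost and contributing nothing: 90 × 0.90 = 81 patients, and 12 × 81 = 972.

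Patients lost part-way would still give some answers, so 10% loss puts the count between 972 and 1,080. If the form in use says knee, the count is 0.

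**The case against.** The strongest reply is that this is a journal article and not the questionnaire. The printed form and the additional file are not at hand. The lead-in is the authors' own narrative and is wrong as well, which suggests a paragraph carried over from hip text, and such a carry-over says little about what patients were handed. This stands. A reader might infer that patients were in fact asked about their hips; the article does not show that.

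A reader might also infer that the comparison between arms is biased. The article does not support this either. The wording would be the same in both arms. Patients complete the questionnaires at follow-up after their knee operation, alongside knee-specific measures, so many could well read the item as being about the knee. Noise and missing answers are possible, but their extent is unknown. The count of 1,080 is a ceiling on responses and not an estimate of an effect.

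Nor can it be said that the instrument is invalid for knees. The word hip in the validation sentence may be part of the same carry-over.

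None of this removes the error in the text. The items are given as the outcome definition, and nothing in the article corrects them.

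**Conclusion.** The point holds as a contradiction within the article. A listed secondary outcome is defined for the wrong joint in its lead-in and in all four items, and the claim that it is validated is supported only for the hip.

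The size is conditional. At most 1,080 responses are involved, or 972 if a tenth of patients contribute none, and this assumes that the form carries the printed wording. If the form says knee, this is a text correction only. The change from baseline to 6 months in WOMAC function, which is the primary outcome, and the sample size built on it do not depend on these items.

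It should be corrected, and the form checked promptly. Trial status dates recruitment from May 2019 and final follow-up to December 2022, so forms may already have been in use.

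**What to change.** 1. Change hip to knee in the lead-in sentence and in the four satisfaction items.
2. Check the questionnaire actually in use against the corrected text.
3. If hip-worded forms have been completed, correct the form for the remaining visits, flag the affected responses, and report satisfaction with and without them. Sending a corrected form later would not recover how satisfied a patient was at a visit already past.
4. Before editing the validation sentence, check which joint reference 23 covers. If it covers the knee, correct the sentence. If it covers the hip only, leave the hip in that sentence and describe the knee version as adapted in both the Objectives and the Outcome measures. Replacing the word without checking could create a validation claim that has no source.

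The cost is a handful of word changes, one look at the cited source and one look at the form. If hip-worded forms were used, add a flag in the database and one sensitivity analysis.
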